## 2. SYNOPSIS OF STUDY DESIGN AND PROCEDURES

***This is a summary of the study design as described in the study Protocol (version 3.0, 6th March 2023) to inform this statistical analysis plan. For all other purposes please ask to see the current version of the protocol.***

### 2.1. TRIAL OBJECTIVES AND AIMS

The RAPID-TEST trial aims to evaluate the use of a rapid respiratory microbiological point-of-care-test POCT for suspected respiratory tract infection (RTIs) in primary care.

---

#### 2.1.1. PRIMARY CLINICAL OBJECTIVES

To investigate whether the use of a rapid POCT can reduce same-day antibiotic prescribing for children and adults presenting to primary care with RTIs where the Study Clinician and /or patient believes antibiotic treatment is, or may be, necessary. This is assessed by whether any antibiotic was prescribed for a RTI at appointment 2 of day 1.

---

#### 2.1.2. SECONDARY CLINICAL OBJECTIVES

To investigate whether the use of a rapid POCT impacts on patient symptoms and antibiotic and antiviral consumption, as reported in the participant diary. The key secondary measure is derived from the symptom diary: the mean symptom score on days 2 to 4.

To investigate whether the use of a rapid POCT impacts on primary care presentations for RTI, antibiotic and antiviral prescriptions, and hospital admissions for RTI by review of the participants' primary care records.

To investigate whether the use of a rapid POCT impacts on patient beliefs and intentions, including participant confidence in the clinical management of the infection (reported on day 1) and participant intention to consult for similar illnesses in the future (reported at 2 months).

---

#### 2.1.3. PRIMARY MECHANISTIC OBJECTIVES

To determine whether there are overall (POCT test vs. No POCT test) and differential (virus detected vs. not detected) effects with respect to reducing number of participants for whom the Study Clinician believes antibiotics are necessary (as a mediator of the primary clinical outcome).

---

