Where the outcome measure is GP belief that an antibiotic is necessary (assessed immediately after the POCTRM result is made available), the interaction term will capture the evidence of impact of the test result on GP belief, allowing for the different impacts of a virus being detected and no virus detected. If there is evidence the POCTRM result impacts GP beliefs and prescribing, the association between beliefs and prescribing will be examined for consistency with GP belief mediating between the test result i.e. how do GPs interpret and use the test information, and the prescription of an antibiotic. We anticipate a greater probability of an antibiotic prescription when the GP has greater confidence an antibiotic is necessary, in

which case we may infer that the POCTRM reduces antibiotic prescribing by identifying a potential viral cause in the majority of cases leading to high confidence that an antibiotic will be of benefit for fewer participants than in the comparison group.

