#### 4.8. MECHANISTIC ANALYSIS

The POCTRM result is a key potential mechanism on the causal pathway between availability of the POCTRM, the clinician's belief that an antibiotic is necessary and the decision to prescribe an antibiotic. We will conduct a mechanistic analysis on the per protocol sample. An interaction term will capture any difference in the effect of the test result on prescribing between the two randomly allocated groups who do and do not have the test result available to inform the clinical decision. In the logistic regression model:

$$\text{Log odds(antibiotic prescribed)} = [\text{Group}] + [\text{Virus detected versus not detected}] + [\text{Interaction}]$$

"Virus detected versus not detected" will be as determined by the practice POCTRM machine in the intervention group (i.e. the result that will inform the general practitioner's decision making), and as detected by the central study POCTRM machine in the comparison group. Note that any finding including detection of an atypical bacteria will be coded as "virus not detected" as better reflecting the likely influence of this result on decision making.

The null hypothesis for the interaction term is that the 'virus detected/not detected' result has the same effect on prescribing in the POCTRM (have the virus detected/not detected result to inform their prescribing decision) and comparison groups (do not have the result to inform their prescribing decision). The interaction term in the analysis model separates the effect of the POCT result from study clinicians' underlying ability to appropriately diagnose the need for an antibiotic without the POCTRM result. Whilst the POCT result is revealed to study clinicians and intervention group participants post-randomisation, the proportions of viral and bacterial infections will have been balanced by the randomisation, such that an interaction test from the standard regression model will give evidence of the causal role of the POCTRM test result (**Table 2**, see Section 5).

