Clinician and participant views, pre-randomisation, will be tabulated by allocated group for the full analysis set (**Supplementary Table 3a, 3b; Supplementary Table 4a**, see Section 5). Clinician views, post-randomisation, will be tabulated by allocated group for the per protocol set, and the null hypothesis of no difference in the population in views between the two groups will be tested using an ordered logistic regression model (**Supplementary Table 4b**, see Section 5). Participant views, post-randomisation, will be tabulated by allocated group for the full analysis set, and the null hypothesis of no difference in the population in views between the two groups will be tested using an ordered logistic regression model (**Supplementary Table 3c, 3d**, see Section 5).

The result of the POCTRM test for each participant in the intervention group will be presented, with the probability of a prescription of antibiotic or of a antiviral for each observed result (**Supplementary Table 5**, see Section 5).

The change in response to the question “I believe an antibiotic is needed to treat the patient’s illness” for clinicians in the per protocol set is tabulated for the three groups, POCTRM virus detected, POCTRM no virus detected, no POCTRM group (**Supplementary Table 6**, see Section 5).

The aim of the primary results paper is to present information on the nature and magnitude of the effect of the POCTRM on clinical outcomes, and upon potential mechanisms for that impact on outcomes. These results will guide the scope and approach to a causal analysis of potential mechanisms for any clinical benefit of POCTRM, to be reported in a separate paper.

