aOrdinal logistic regression model, adjusting for baseline participants' views, age and chronic lung disease status

**Supplementary Table 5.** POCTRM result for participants allocated to the intervention group, with subsequent prescription of antibiotics and antivirals.

|                                 | Number of cases
(N=)                              | Number prescribed
antibiotic at
appointment 2             | Number prescribed
antiviral at
appointment 2              |
|---------------------------------|------------------------------------------------------|-----------------------------------------------------------------|-----------------------------------------------------------------|
|                                 | n (% of participants
in POCT RM group) | n (% of participants
with this POCT RM
result) | N (% of participants
with this POCT RM
result) |
| No valid result                 | XX (XX%)                                             | XX (XX%)                                                        | XX (XX%)                                                        |
| No microbe detected             | XX (XX%)                                             | XX (XX%)                                                        | XX (XX%)                                                        |
| Single microbe detected  |                                                      |                                                                 |                                                                 |
| Bordetella pertussis            | XX (XX%)                                             | XX (XX%)                                                        | XX (XX%)                                                        |
| Bordetella parapertussis        | XX (XX%)                                             | XX (XX%)                                                        | XX (XX%)                                                        |
| Chlamydia pneumoniae            | XX (XX%)                                             | XX (XX%)                                                        | XX (XX%)                                                        |

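### The SAP does not estimate or test the differential (virus vs. no virus) effect on clinician belief that its primary mechanistic objective asks for, and the footnote to its clinician-belief test names participants' baseline views

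*Combined protocol and SAP*

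**What the plan says.** SAP 2.1.3, matching protocol Table 3, states one primary mechanistic objective in two parts: "overall (POCT test vs. No POCT test) and differential (virus detected vs. not detected) effects". The outcome is the number of participants for whom "the Study Clinician believes antibiotics are necessary (as a mediator of the primary clinical outcome"). Protocol Appendix 1 identifies this as clinician question 1, asked at Step 2 (Appointment One) and Step 5 (after allocation and, in the intervention arm, after the test result).

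Protocol 10.2 gives a logistic model with group, result and interaction for this belief, and says that "the interaction term will capture the evidence of impact of the test result on GP belief".

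SAP 4.8 uses that structure for a different outcome: "An interaction term will capture any difference in the effect of the test result on prescribing between the two randomly allocated groups". Virus status comes from the practice machine in the intervention arm "and as detected by the central study POCT" machine in the comparison arm.

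For clinician belief the SAP has two items:

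- "Clinician views, post-randomisation, will be tabulated by allocated group for the per protocol set", with an ordered logistic test of group (Supplementary Table 4b). The footnote describes the model as "adjusting for baseline participants' views, age and chronic lung disease status". The table has a p-value column but no effect estimate.
- The change in question 1 from before to after randomisation "is tabulated for the three groups": intervention with virus, intervention without virus, and all controls together (Supplementary Table 6). No test or estimate is attached.

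A causal analysis of mechanisms is left to a separate paper.

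**The concern.** The trial names clinician belief as its primary mechanistic outcome and asks whether the test result, not merely having a test, shifts that belief. That is the differential part. Estimating it needs the contrast between virus and no-virus participants in the intervention arm, set against the same contrast in controls, whose clinicians never saw a result. Controls matter because clinicians may already tell some viral cases apart without the test, which protocol 10.1.2 allows for.

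The protocol supplies this model and the SAP omits it for belief. If the SAP is followed, the report will have a p-value for the overall effect on belief, a descriptive table for the differential effect, and a tested interaction only for prescribing. Any belief interaction fitted later would lack a pre-specified form.

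The covariate slip is smaller but sits in the one clinician-belief test that the SAP keeps. The natural baseline for a clinician's Step 5 answer is that clinician's Step 2 answer, which is collected and tabulated in Supplementary Table 4a.

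**Working it through.** **1. Objective against analysis**

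| Part of the objective | Protocol 10.2 | SAP 4.8 and Section 5 |
|---|---|---|
| Overall effect on clinician belief | Group term | Tested by group, per-protocol set, p-value only (Table 4b) |
| Differential effect on clinician belief | Group × result interaction | Tabulated in three groups, controls unsplit, no estimate or test (Table 6) |
| Differential effect on prescribing | Group × result interaction | Tested, per-protocol set (SAP Table 2) |

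The middle row is the gap. The data for it exist. SAP 4.8 already assigns a virus result to controls for the prescribing model, and clinician question 1 is asked at both steps in both arms. The SAP's closing list of analyses planned outside the document does not include a belief interaction.

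**2. The plan's own power figure**

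Protocol 10.1.2 states more than 90% power for the interaction on prescribing, with 244 per group, at a 60% relative reduction among virus-positive participants. Inputs from Table 10: 60% virus, 40% no virus; control prescribing 50% (virus) and 75% (no virus); P1 = 90% (Scenario One) or 75% (Scenario Two); P2 = 0.4 × 50% = 20%.

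- Cell sizes per arm: 0.4 × 244 = 97.6 (no virus) and 0.6 × 244 = 146.4 (virus).
- Interaction = log odds ratio (virus) − log odds ratio (no virus). Its variance is the sum over the four cells of 1/[n p(1 − p)].
- Scenario Two: odds ratios 0.25 and 1, so the interaction is ln 0.25 = −1.386. Variance 0.179, SE 0.423, z = 3.27. Power = Φ(3.27 − 1.96) = 91%.
- Scenario One: odds ratios 0.25 and 3, so the interaction is ln(0.25/3) = −2.485. Variance 0.238, SE 0.488, z = 5.09. Power above 99%.

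Simulation with the protocol's likelihood ratio test gives 90.5% and 99.9%. The stated figure reproduces.

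**3. Can the overall test stand in for the differential one?**

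Take illustrative belief rates (assumed; the documents give none): intervention 90% (no virus) and 40% (virus), control 75% and 50%.

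- Intervention overall: 0.4 × 90% + 0.6 × 40% = 36% + 24% = 60%.
- Control overall: 0.4 × 75% + 0.6 × 50% = 30% + 30% = 60%.
- Odds ratios: no virus (0.9/0.1)/(0.75/0.25) = 3; virus (0.4/0.6)/(0.5/0.5) = 0.667; ratio 0.667/3 = 0.22.

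The group comparison has nothing to detect. The interaction has 91% power by simulation (89% by the formula above: SE 0.474, z = 3.18). The two parts of the objective are separate questions.

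**4. Would the restored test be worth running?**

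If dichotomised belief followed the Table 10 prescribing rates (an assumption), simulated power at a 60% relative reduction in Scenario Two would be 92% with 257 per group, 90% with 244, 89% with 232 and 87% with 220. The last two are assumed losses of about 5% and 10% from 244. In Scenario One it exceeds 99% throughout. Protocol 10.1.2 expects more power for mechanisms measured on a scale, which favours keeping all five levels.

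**5. The Table 4b covariate**

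The footnote is word for word that of Supplementary Tables 3c and 3d, which report participant views and where it is correct. The text of SAP 4.8 names no covariates for the clinician model, so the footnote is the only instruction.

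**The case against.** **Table 6 already speaks to the question.** It cross-tabulates the clinician's answer before and after the result, separately for virus and no virus. A reader might infer that the trial can say nothing about how the result changes belief. That goes too far: the change is described in the intervention arm, starting from the Step 2 answer. What is missing is an estimate, its uncertainty, and the matching control contrast.

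**The analysis may come later.** The SAP defers causal mechanism work to another paper, and the protocol model still stands. But the deferral names no model and says the results will shape the approach, so it does not pre-specify this test.

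**The footnote is a slip.** Probably so. It still needs correcting, but it is not evidence of a deliberate choice to drop the better covariate. It also concerns clinician belief only; participant views are tested properly in the full analysis set.

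**The per-protocol set is declared** (SAP 3.1) as the basis for mechanisms. That stands for the interaction. For the overall comparison, the valid-result criterion applies to the intervention arm only, so the set is not fully protected by randomisation. Intervention clinicians must wait for a result before giving Step 5 views (protocol 6.6.3), so a full-set version may add few participants. It belongs as a sensitivity analysis.

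**Virus status is measured differently by arm.** A reader might infer that this creates a spurious interaction. The documents give no miss rate for the central test, which uses the same panel and system, and the practice result is chosen because it is what the clinician saw. Agreement between practice and central results is already to be assessed in the intervention arm. This supports at most an optional sensitivity analysis.

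**Conclusion.** The concern holds as a mismatch between objective and analysis, and it rests on the text rather than on any wrong number. The differential half of the primary mechanistic objective has a model in the protocol but only a descriptive table, without a control contrast, in the SAP. The overall test cannot substitute: with the illustrative rates its effect is exactly zero while the interaction has about 91% power. That example and the power figures for belief rest on assumed belief rates; the gap itself does not.

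The Table 4b footnote is wrong as written, most likely through copying. The population point is minor and merits a sensitivity analysis.

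The documents do not support a claim that the retained prescribing interaction is biased or underpowered: its stated power reproduces at the effect size the protocol specifies. The primary clinical analysis is not touched. The change should be made because it decides whether the stated primary mechanistic question gets a pre-specified answer.

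**What to change.** In SAP 4.8 and the matching tables:

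1. Carry over the protocol's belief interaction as an ordinal logistic model of Step 5 clinician question 1 on group, virus result, group × result, Step 2 clinician question 1, age group and chronic lung disease. Use the virus result as SAP 4.8 already defines it, and report the interaction estimate with its confidence interval.
2. Correct the Supplementary Table 4b footnote to baseline clinician views.
3. Split the control group of Supplementary Table 6 by central result.
4. Add a full-analysis-set version of the overall clinician-belief comparison as a sensitivity analysis.

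Optionally, repeat the interaction models with the central result in both arms. State two limits: protocol 6.6.2 sends the laboratory the remaining sample in the intervention arm but the whole swab in control, so measurement is not fully equalised; and replacing the result the clinician saw may dilute a true effect.

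The cost is SAP wording, one extra main model, one sensitivity model and one re-cut table, all on data already planned. Under SAP Section 1 the change would be described and justified as an amendment in the final report.

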#### 2.1.4. SECONDARY MECHANISTIC OBJECTIVES

To describe the effect of POCT results on Study Clinician and participant (or parent/carer if the participant is <16 years) beliefs and intentions with respect to the necessity, and benefits, of prescribing antibiotics for the respiratory infection, and confidence in the value of the POCT to guide the prescribing decision and explore the relationship between Study Clinician and participant beliefs, attitudes and intentions with antibiotic prescribing and consumption.

## 2.2. TRIAL DESIGN AND SETTING

A multicentre, individually randomised control trial with mixed-methods investigation of microbial, behavioural and antibiotics mechanisms. Participant will be randomised on a 1:1 basis to either intervention group (POCT test) or control group (No POCT test). They will undergo follow-up until symptoms resolution or 28 days post-randomisation as well as review of their primary care medical records at 2 months and 6 months.

The trial duration is expected to be 38 months in total, which included 2 waves. The trial is planned to set up approximately 8 general practices (sites) during Wave 1 for Winter 1 period (the internal pilot study) followed by a Summer 1 period. The initial 8 sites will be closed gradually during Summer 1 period while another 8 sites will be opened as Wave 2 (from Summer 1) and continued for Winter 2 and Summer 2. Study general practices will be recruited from those served for routine laboratory testing by one of the following four hospitals: Southmead (North Bristol), the Bristol Royal Infirmary, Royal United Hospitals (Bath) and Weston General (Weston-super-Mare).

## 2.3. ELIGIBILITY CRITERIA

In brief, participants must be:

- i. Aged  $\geq 12$  months on the day of presentation to primary care
- ii. Presenting to primary care for the first time in this episode, and within 21 days of illness onset, with a Study Clinician suspected acute respiratory infection.
- iii. Study Clinician or patient/parent/carer believes antibiotic treatment is, or may be, necessary (either Study Clinician or patient/parent/carer must answer "strongly agree", "agree" or "neither agree nor disagree" to question 1 from the Study Clinician views and question 1 from Participants Views detailed in Appendix 1)

The key exclusion criteria are:

- i. Patient known to have cystic fibrosis
- ii. Patient requires hospital admission
- iii. Previous participation in the current RAPID-TEST trial
- iv. Participation in another study of RTI  $\leq 6$  weeks prior to randomisation

## 2.4. DESCRIPTION OF INTERVENTION

Eligible and consented participants will have Appointment One (pre-randomisation) and Appointment Two (post-randomisation) with Study Clinician. After Appointment One, nasal and throat swabs will be taken using swab collection kit. Swab samples from intervention group will then be analysed using the practice's BioFire® FileArray® Torch 1 system immediately after randomisation. At Appointment Two, the Study Clinician will contact the participant to inform them the allocation, result of POCT test (for intervention group) and to discuss treatment. They will be advised to use POCT result (for intervention group) as a guide to clinical decision making i.e. antibiotic prescribing. Whether or not the participant is prescribed an antibiotic at appointment two is the primary outcome measure.

## 2.5. RANDOMISATION PROCEDURES

The randomisation sequence will be generated by Sealed Envelope and will be stratified by age (<16 years vs. ≥16 years) and chronic lung disease (present vs. absent). Allocations will be provided online to the Study Clinician via the Sealed Envelope website.

## 2.6. BLINDING

The participants and the Study Clinicians will not be blinded to the allocation of treatment group. They will be informed the allocation group after randomisation. The BTC trial statistician will be unblinded in-order to report to the Data Monitoring Committee, while the senior statistician will remain blinded. The central trials team will remain blinded, including the chief investigator and trial manager.

## 2.7. SAMPLE SIZE CALCULATION

Assuming an antibiotic prescribing rate of 60% in the control group, 244 participants per group will allow a true reduction to 45% in the POCT group to be detected with 90% power at 5% significance. A total randomisation target of 514 will allow for 5% attrition. This number will provide at least 90% power to detect the same absolute difference if the antibiotic prescribing rate is found to be higher or lower than 60% in the control group.

If the POCT results in fewer antibiotic prescriptions, we wish to demonstrate non-inferiority of the POCT in terms of not increasing mean symptom severity at days 2 to 4 to a clinically significant extent. Assuming 80% completion of Trial Diaries (as previously achieved in adults and children) we will have data for symptom severity at 2 to 4 days in 206 participants per group. Data on 7,000 adults and children managed without POCT indicates a mean symptom severity at days 2 to 4 of 2.3 (standard deviation 1.5). We know this measure's distribution is positively skewed and have used a calculation that accommodates this (assuming equal skew in both groups, quantified as a coefficient of variation of 0.7). Assuming, in truth, no difference between groups, 206 participants in each group will give 90% power for a one-sided 95% confidence interval to exclude increases in the average symptom score of 20% or more.

